### Study sample

To calculate sample size, the following formula will be used:

$$ N=\frac{{\left({U}_{\alpha }+{U}_{\beta}\right)}^2\times 2P\left(1-P\right)}{{\left({P}_1-{P}_2\right)}^2} $$

where α = 0.05, β = 0.1, and then U_0.05_ = 1.96, U_0.1_ = 1.28. According to a previous study in China, the proportion of daily per capita salt consumption ≤6 g was 37.91% and the proportion increased to 45.91% after using salt-control spoons in participating households [16]. Thus, in this study, the increase in low salt consumption (≤6 g/d) with SALTCHECKER from about 38% (*P*_*1*_) to some 46% (*P*_*2*_), *P* = (*P*_1_ + *P*_2_)/2 = 0.42 was assumed. The sample size is calculated to be 799 cases. According to some similar salt-limiting trials, the dropout rate was 0.5–5% [18, 40–42]. And sampling error and invalid questionnaires may be 10–15%. Therefore, it was assumed 10–20% should be added on the basis of the estimated sample size, so 879–959 participants will be needed. The data of the tabulation on the 2010 population census of the People’s Republic of China (No. 1) indicated that the average household size in Chongqing is 2.70 (person/household) [43]. Therefore, 300 households’ main cooks in each of the intervention group and control group will be investigated in this study.

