### Analysis strategy

Statistical analyses will be conducted using SPSS version 22.0 (IBM Corp, Armonk, NY, USA). Descriptive statistics will be calculated for all the variables under examination. The counting data will be described by frequency and percentile, and the metrological data description will use mean, standard deviation and median. The demographic characteristics of the household members (e.g. age, gender, ethnicity, occupation, marital status, education level, height, weight and health status) will be analysed to examine the influencing factors of the household salt monitoring system by using multivariate regression analysis. Linear mixed models, generalized estimating equations (GEE) or t-test will be used to examine the predictors of added salt intake of each household member and salt consumption-related KAP of the household’s main cook and the moderators, mediators of the intervention effects. Correlation analysis will be used to test the link between the score of salt consumption-related KAP and daily added salt intake of each household member. Meanwhile, we will analyse the time trends of the daily added salt intake of each household member during the study period. The level of significance will be set at < 0.05. For the qualitative data analysis, the audio recordings will be transcribed verbatim by trained transcribers. Content analysis of the qualitative information gathered will be done using MAXqda. In addition, if there is enough data acquired about blood pressure, analysis of the impact of the system on blood pressure will be considered.

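### The sample size counts household members as independent cases with no design effect, so the stated 90% power is not delivered at any material within-household correlation, and the analysis section leaves member-level tests open that ignore the household

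*Protocol article*

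**What the plan says.** The protocol's Study sample section sets the error rates ("where α = 0.05, β = 0.1, and then U_0.05_ = 1.96, U_0.1_ = 1.28") and takes its effect from an earlier salt-spoon study, in which "the proportion of daily per capita salt consumption ≤6 g was 37.91% and the proportion increased to 45.91% after using salt-control spoons". It rounds these to 38% and 46% with a mean of 0.42, and concludes: "The sample size is calculated to be 799 cases". It then allows for loss ("it was assumed 10–20% should be added on the basis of the estimated sample size, so 879–959 participants will be needed"), cites a census figure that the "average household size in Chongqing is 2.70 (person/household"), and settles on 300 main cooks, that is 300 households, in each group. No ICC or design effect appears.

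Other sections fix the structure of the data:

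- Randomization and blinding allocates households 1:1 through the main cook, 300 per group.
- Primary outcomes defines the salt outcome per household member, at baseline, 3 and 6 months.
- The Development of SALTCHECKER gives the rule for a member's value: the household's 30-day salt use, times that member's share of the household's standard daily number, divided by 30. One container is weighed per household.
- Analysis strategy states: "Linear mixed models, generalized estimating equations (GEE) or t-test will be used to examine the predictors of added salt intake of each household member". The same sentence covers the cook's KAP score. A later sentence adds a correlation between the KAP score and the members' daily salt values. The household is not named as a cluster or random effect.

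**The concern.** The household is both the unit of allocation and the unit of measurement, but the person is the unit that is counted. Members of one household share the cook, the intervention and a single weighed total. A second or third member therefore brings a different share of the same measurement, not a new one. A formula for independent persons credits the trial with more information than 300 households per arm can supply.

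Two things are at stake. First, the only power statement in the protocol, which supports a primary outcome, is too favourable. Second, the Analysis strategy leaves it possible to run a t-test or a correlation with one row per member. Standard errors would then be too small, and an ineffective intervention or an absent KAP–salt link could too easily appear significant. The correlation is especially exposed, because one cook's score would be repeated across every member of the household.

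**Working it through.** **Inputs from the protocol.** Critical values 1.96 and 1.28; P1 = 0.38, P2 = 0.46, P = 0.42; mean household size m = 2.70; 300 households per arm.

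**Input not in the protocol.** The within-household ICC. It is assumed here over 0.1 to 1.0.

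**Step 1: reproduce the plan's figure.** N = (1.96 + 1.28)² × 2 × 0.42 × 0.58 / 0.08² = 799.13. The stated 799 is reproduced. This formula gives the number per group.

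**Step 2: how persons become households.** 799 / 2.70 = 296 households per arm, in line with the planned 300; 300 × 2.70 = 810 members per arm. If those 810 were independent, power would be Φ(0.08 × √(810 / 0.4872) − 1.96) = 90%, where 0.4872 = 2 × 0.42 × 0.58. So the 90% depends on treating members as independent.

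**Step 3: allow for the household.** With equal household sizes:

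- Design effect DE = 1 + (2.70 − 1) × ICC
- Effective n per arm = 810 / DE
- Power = Φ(0.08 × √(effective n / 0.4872) − 1.96)
- False-positive rate of a test that ignores the household = 2 × (1 − Φ(1.96 / √DE))
- Households per arm for 90% power = 799.13 × DE / 2.70

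| Assumed ICC | DE | Effective n per arm | Power, no loss | False-positive rate on member rows | Households per arm for 90% power |
|---|---|---|---|---|---|
| 0.1 | 1.17 | 692 | 85% | 7% | 347 |
| 0.3 | 1.51 | 536 | 76% | 11% | 447 |
| 0.5 | 1.85 | 438 | 67% | 15% | 548 |
| 1.0 | 2.70 | 300 | 51% | 23% | 800 |

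These powers assume no loss. The plan's own enlarged target of 879–959 would need 879 / 2.70 = 326 to 959 / 2.70 = 355 households per arm even without clustering, so the loss-free figures are generous to the plan.

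**Step 4: which part of the ICC range is plausible.** The allocation rule was simulated with assumed spreads: household sizes 1 to 5 with mean 2.7, log-normal household salt per person with log SD 0.4 to 0.6, and log-normal member weights with log SD 0 to 0.35. The ICC was about 0.5 to 1.0 for intake and 0.34 to 1.0 for a low-intake indicator holding for 42% of members, the plan's mean proportion. This is illustrative only. It makes high values plausible but does not establish one.

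**Step 5: what 300 households per arm can detect at 90% power, before loss.**

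- Household-level salt, one value per household: (1.96 + 1.28) × √(2 / 300) = 0.26 SD.
- Proportion at or below 6 g/d, ICC near 1 (effective n 300): starting from 38% with mean proportion about 0.445, 3.24 × √(2 × 0.445 × 0.555 / 300) = 0.13, or about 13 percentage points.
- The same proportion at ICC 0.5 (effective n 438): with mean proportion about 0.435, 3.24 × √(2 × 0.435 × 0.565 / 438) = 0.11, or about 11 points.

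The plan assumes 8 points.

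**The case against.** The strongest case on the other side has four parts.

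*The listed methods include the right ones.* Mixed models and GEE are standard for clustered data. The sentence covers KAP as well as salt, and a t-test is sound for KAP because there is one cook per household. It also speaks of predictors, moderators and mediators and does not say which method tests the group comparison. This stands to a large extent: a reader might infer that every permitted analysis treats members as independent, and the text does not support that. What remains is that the t-test is listed for member salt too, the correlation is specified against member intake, and no household term is attached to anything.

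*The ICC is unknown.* This stands. A reader might infer that power is known to be 51–67%, or that the ICC is near 1 by construction. Neither follows. Members' shares differ, and members of one household can fall on either side of 6 g/d, so the indicator can have a lower ICC than intake itself. The result has to be given as a range.

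*The false-positive rate can be overstated.* With equal household sizes the ceiling is 23%. Reaching 25% needs a further assumption about unequal sizes (for example a coefficient of variation of 0.4 with ICC 0.9), and the protocol gives no size distribution.

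*It is a pilot in a condensed article, and an analysis plan may supply the detail.* This does not remove the point. The Design section does use the word pilot, but stage 2 is there to evaluate effectiveness, and the Study sample section fixes both the size and 90% power. A later analysis plan can choose a valid clustered method, but that method then has the reduced power.

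**Conclusion.** The point holds for the sample size without reservation as to kind: members are counted as independent, no design effect is applied, and the stated 90% is not reached at any material ICC. Even at 0.1, about 347 households per arm would be needed against 300 planned. Its size depends on an ICC that the documents do not give: about 85% power at 0.1, 76% at 0.3, 67% at 0.5 and 51% at 1.0, with equal household sizes and no loss. Higher values are plausible because members share one measured total.

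For the analysis, the fault is narrower. The section allows valid methods but also leaves open a member-row t-test and correlation. If either were used, its false-positive rate would be about 7% to 23% over the same ICC range. KAP as an outcome is not affected. Because this concerns a primary outcome and the protocol's only power statement, it should be corrected before analysis.

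**What to change.** In Analysis strategy, make the household either the unit or the cluster for salt: analyse household added salt per standard person-day, or keep member rows with a household random intercept or a GEE clustered on household. State that the t-test is not used on member rows; it may stay for KAP. Run the KAP–salt correlation on one row per household.

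In Study sample, restate what 300 households per arm can show: about 90% power for a 0.26 SD difference in household-level salt. If the 6 g/d proportion is kept, state about 13 percentage points for an ICC near 1 or about 11 points for 0.5, all before loss, with the ICC labelled as an assumption.

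The cost is a change of wording in two sections and a less favourable stated power or detectable difference. No extra participants are required.

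### The planned 300 households per arm hold about 1.4% of spare members, not the 10–20% allowance that the sample-size section says was added

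*Protocol article*

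**What the plan says.** All the steps stand in the protocol article, Methods/Design, Study sample.

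- The formula is the two-proportion one with 2P(1−P) in the numerator. Its constants are given as "where α = 0.05, β = 0.1, and then U_0.05_ = 1.96, U_0.1_ = 1.28".
- The proportion of people at or below 6 g of salt a day is assumed to rise from 38% to 46%, so P = 0.42.
- The result is given as "The sample size is calculated to be 799 cases", without saying whether this is per group or in total.
- Similar trials are said to have lost 0.5–5% to dropout, and a further 10–15% is put down to sampling error and invalid questionnaires. From this, "it was assumed 10–20% should be added on the basis of the estimated sample size, so 879–959 participants will be needed".
- A census figure of 2.70 persons per household in Chongqing follows, and then the conclusion: "Therefore, 300 households’ main cooks in each of the intervention group and control group will be investigated in this study".

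The Recruitment section (600 main cooks selected) and the Randomization and blinding section (1:1, 300 households in each group) repeat the final number. Neither provides for over-recruitment.

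**The concern.** The conclusion is introduced as a consequence of the inflated range and the household size, but no step leads from 879–959 to 300, and the division by 2.70 does not give 300. A reader would take it that 300 households per arm already cover 10–20% of losses and so protect the 90% power. If they do not, the article claims a safeguard that the chosen size lacks, and the quoted power holds only if almost nobody is lost.

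**Working it through.** **Inputs (all from Study sample).** U values 1.96 and 1.28; P1 = 0.38, P2 = 0.46, P = 0.42; addition 10–20%; 2.70 persons per household; 300 households per arm.

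**1. Reproduce the plan's figure.**
N = (1.96 + 1.28)² × 2 × 0.42 × 0.58 / 0.08² = 799.1. The plan's 799 is reproduced. (The unrounded rates 37.91% and 45.91% give 798.7.)

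**2. Per arm or total?**
The factor 2P(1−P) is the sum of the two arms' variances when each arm has N members, so N is per arm and the total is 2 × 799 = 1,598. A power check agrees, using

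power = Φ{ [0.08·√n − 1.96·√(2 × 0.42 × 0.58)] / √(0.38 × 0.62 + 0.46 × 0.54) }, with n per arm.

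- n = 799: 90.0%, which matches β = 0.1.
- n = 399.5 (799 taken as the total): 63.0%, which does not.

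**3. The addition.**
799 × 1.10 = 878.9 and 799 × 1.20 = 958.8. The plan's 879–959 is reproduced, per arm.

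**4. Convert to households per arm.**

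| Members per arm | ÷ 2.70 | Households, rounded up |
|---|---|---|
| 799 (no addition) | 295.9 | 296 |
| 879 (10% added) | 325.6 | 326 |
| 959 (20% added) | 355.2 | 356 |

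The plan's own arithmetic needs 652–712 households in all, against 600 planned. The gap is 26–56 households per arm.

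**5. What 300 households supply.**
300 × 2.70 = 810 members per arm. 810 − 799 = 11, and 11/799 = 1.4%. Losses above 1 − 799/810 = 1.4% take an arm below 799.

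**6. Power for 38% versus 46%, starting from 810 per arm and treating members as independent.**

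| Loss | Members left per arm | Power |
|---|---|---|
| 0% | 810 | 90.4% |
| 5% | 769.5 | 88.9% |
| 10% | 729 | 87.3% |
| 15% | 688.5 | 85.3% |
| 20% | 648 | 83.2% |

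**7. Why these are upper bounds.**
Households are randomized, and each member's intake is apportioned from one household total (the Development of SALTCHECKER section). The article gives no intra-household correlation, so the following range is an assumption. With the design effect 1 + (2.70 − 1) × ICC, an ICC of 0.05 gives 1.085 and an ICC of 0.5 gives 1.85. Dividing 810 by these gives power of about 88% and 67%, before any loss.

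**The case against.** **The loss of power is modest, and 83% is the pessimistic end.** This stands. Most of the 10–20% comes from sampling error and invalid questionnaires. The questionnaire is the main cook's KAP form, while the sensor records salt use automatically, so an invalid form need not remove salt data. With dropout alone, at most 5%, power is about 89%. Some salt data can still be lost: outlying measurements are to be excluded (Data of the daily added salt intake integrity), and apportioning salt to members needs information entered in the mini programme. The Design section also calls the study a pilot. All this lowers the severity, but the conclusion still does not follow from the printed steps.

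**The article condenses a fuller protocol.** This does not help, because nothing is claimed to be missing. The steps are printed and the result disagrees with them.

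**600 × 2.70 = 1,620 exceeds 959, so the trial is larger than needed.** This would require 799 to be the two-arm total, which the formula and the 63% power exclude. On that reading 163–178 households per arm would follow, which is not 300 either.

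**Stronger readings that a reader might infer.**
- That 879–959 is itself wrong and should be 799/(1 − d). The plan says that a percentage is added and computes that correctly. Dividing by the retained fraction is a preference and does not correct an error.
- That the basis of 799 cannot be known. The missing label is a wording gap, and the formula settles the matter.
- That the authors rounded up the uninflated 296. The number 300 matches this, but the article does not say how it was reached.

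**Conclusion.** The point holds, as something that should be corrected. The formula yields 799 per arm, the plan's own addition raises this to 879–959 per arm, and that needs about 326–356 households per arm. The planned 300 supply about 810 members, an allowance of 1.4% where 10–20% is stated.

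Under the plan's own 10–20% loss, power for the 38% versus 46% comparison is about 87–83%, and about 89% with 5% dropout alone. This assumes that the census average of 2.70 applies to the enrolled households, that the whole loss falls on members' salt data, and that household members are independent. The last assumption makes the figures upper bounds.

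It would go too far to say that there is no allowance at all, or that the missing allowance by itself leaves the trial badly underpowered. A small margin exists, and on the independence assumption power stays above 80%. Nor are 326–356 households shown to be enough: they are only the plan's own arithmetic carried through, without clustering.

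**What to change.** In Study sample:

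1. Label 799 as per arm (1,598 in total), and 879–959 as per arm.
2. State that 300 households per arm, about 810 members, carry an allowance of about 1.4% over 799, and remove the implication that the 10–20% is included.
3. Restate the power for 300 households per arm under the plan's own loss assumption. Do this once, with household clustering taken into account and the assumed intra-household correlation stated. The 83–87% above should not be printed as the final figure, since it ignores clustering.

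This is a text correction and does not by itself require more households. The cost is that the quoted power becomes less favourable than 90%.

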### Recruitment

The households will be recruited from Chongqing, China. The study will be advertised in cooperative communities. The following strategies will be used sequentially until the desired sample size is achieved: (1) posters and project leaflets will be distributed; (2) advertisements will be circulated on social media, such as WeChat and Weibo platforms; (3) the project will be presented in the community by project manager or project members in the form of health seminars; and (4) the use, function and advantages of the SALTCHECKER will be demonstrated on-site.

Inclusion criteria: (1) the household’s main cook (involved mainly in household cooking); (2) plan to be living in Chongqing, China for at least 6 months; (3) own a mobile phone (iOS or Android) with Internet access; (4) and agree to have the WeChat mini programme on their mobile phones.

Exclusion criteria: (1) currently using a self-monitoring system or device to track or log living behaviour in household members; (2) having been involved in other salt experiments in household members; and (3) prior history of cognitive or verbal impairments or other diseases that may impact on study participation.

Interested household main cooks or their household members who are already using a self-monitoring system or tracking device will be excluded to avoid the potential confounding effect. The reason is that popular health apps or tracking device frequently implements various behavioural change strategies, which may affect participants’ behaviour.

On the basis of a computer-generated list in the statistical software IBM SPSS version 22.0 (IBM Corp, Armonk, NY, USA), we will randomly select 600 households’ main cooks (who meet the above-mentioned inclusion criteria) from the available household main cooks in the project database. Written informed consent will be collected from all the participants.

### Procedure

A baseline survey will obtain the household demographic information and the salt consumption-related KAP of the household’s main cook. In the test period, the household’s main cook in the intervention group will use the smart salt checker and the salt-limiting WeChat mini programme, while the household’s main cook in the control group will use the smart salt checker with only the weighing function. The data of the daily added salt intake of each household member will be automatically calculated using SALTCHECKER. And the salt consumption-related KAP of the household’s main cook will be assessed at the beginning of the test (i.e. at baseline), the third month and the sixth month after the test. Finally, the effect of the household added salt monitoring system will be evaluated by changes in daily added salt intake of each household member and the salt consumption-related KAP of the household’s main cook. The technological roadmap is shown in Fig. 2.

**Fig. 2 Fig2:**
[figure not shown]
Technology roadmap for this project

### Baseline survey

#### Daily added salt intake of each household member

The front-end sensing system in the SALTCHECKER will automatically obtain the data of the added salt consumption of participating households, and the data will be collected and stored every day. The daily added salt intake of each household member will be calculated based on a formula, described in the Development of SALTCHECKER stage 1 section.

#### Questionnaire survey

A self-administered questionnaire will be designed based on the local and international literature to assess the salt consumption-related KAP of the household’s main cook. The questionnaire will be sent to the household’s main cook through the salt-limiting WeChat mini programme. After the pre-investigation, the reliability and validity of the questionnaire will be tested. The questionnaire will include the following three parts:
Knowledge of salt consumption, such as the daily recommended intake of salt, high-salt diet hazards, recognition of seasonings and food with high sodium, etc. The knowledge of salt consumption is measured (0 = no, 1 = yes, 0 = do not know), and some items require reverse coding.The attitude of salt consumption, such as the attitude to salt-limiting or low-salt diets, awareness and intention of choosing a low-salt diet, etc. will be assessed using the 5-point Likert scale (1 = strongly disagree to 5 = strongly agree) questions.The practice of salt consumption, such as the use of low-sodium salt, proper use of salt-limiting spoons, selection of low-salt food, requiring low-salt food in restaurants, selection of food based on the nutrient list, etc. will be measured using the 5-point Likert scale (1 = strongly disagree to 5 = strongly agree) questions.

A total score will be calculated for the above items, and a high score will represent a high KAP.

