#### Primary outcomes

Daily added salt intake of each household member, assessed at baseline, 3 and 6 months.Salt consumption-related KAP of the household’s main cook, assessed at baseline, 3 and 6 months.

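### As written, the KAP scoring credits 'do not know' on reverse-coded knowledge items and sums 0/1 items with 1–5 items, diluting knowledge gains in a primary outcome by an unstated amount

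*Protocol article*

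**What the plan says.** All the scoring text is in the Questionnaire survey section of the protocol article.

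- Knowledge: "The knowledge of salt consumption is measured (0 = no, 1 = yes, 0 = do not know". The same sentence ends: "do not know), and some items require reverse coding".
- Attitude: "awareness and intention of choosing a low-salt diet, etc. will be assessed using the 5-point Likert scale (1 = strongly disagree to 5 = strongly agree".
- Practice: "will be measured using the 5-point Likert scale (1 = strongly disagree to 5 = strongly agree) questions".
- Overall score: "A total score will be calculated for the above items, and a high score will represent a high KAP".
- Status of the instrument: it is still to be designed, and "After the pre-investigation, the reliability and validity of the questionnaire will be tested".

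The Primary outcomes section lists "Salt consumption-related KAP of the household’s main cook, assessed at baseline, 3 and 6 months".

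The article gives no item counts, no number of reversed items, no separate rule for *do not know* on reversed items, and no weighting or rescaling of the three parts. The Analysis strategy and Discussion sections both refer to the KAP score in the singular.

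**The concern.** There are two separate problems.

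1. **Reverse coding.** The code merges *no* and *do not know* before the reversal. Once both are 0, a reversal cannot tell them apart. On items where *no* is the right answer, a respondent who admits ignorance gets the same mark as one who knows.
2. **Mixed scales.** A plain sum over 0/1 items and 1–5 items gives a knowledge item far less room to move the total than an attitude or practice item.

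Both problems bear on what this trial tries to change. The Background says that knowledge of salt use and its health effects is limited among residents, so *do not know* answers are plausible at baseline. The Intervention section makes conveying knowledge one of two stated purposes of the reports and education. A score that registers no gain from *do not know* to correct on some items, and gives each knowledge item a small range, understates part of what the primary outcome should capture. If answers are stored only as 0/1, the loss cannot be repaired afterwards.

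**Working it through.** The plan states no figure for the KAP score, so there is nothing to reproduce. The check applies the stated rule.

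**Step 1. Reverse coding.** Inputs are the three codes in the Questionnaire survey section. The usual reversal of a 0/1 item is 1 − x.

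| Answer | Code x | Reversed item, 1 − x | Reversed item, if only *yes* and *no* are swapped |
|---|---|---|---|
| *yes* (wrong here) | 1 | 0 | 0 |
| *no* (correct here) | 0 | 1 | 1 |
| *do not know* | 0 | 1 | 0 |

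Changes on a reversed item under 1 − x:

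- *do not know* to correct *no*: 1 − 1 = 0 points.
- *do not know* to wrong *yes*: 0 − 1 = −1 point.
- wrong *yes* to correct *no*: 1 − 0 = +1 point, as it should be.

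On items that are not reversed, *do not know* to correct *yes* gives 1 − 0 = +1. The fault is therefore confined to *do not know* answers on reversed items.

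**Step 2. Size of the dilution.** Let r be the fraction of knowledge items that are reversed (not stated).

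- A cook who answers *do not know* throughout scores r of the knowledge maximum under 1 − x, and 0 if *do not know* is held at 0.
- If moves from *do not know* to correct are spread evenly over items (assumption), the score registers a fraction 1 − r of them.
- For illustration, r = 0.1 loses 10% of those moves, r = 0.3 loses 30% and r = 0.5 loses 50%.

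**Step 3. Mixed scales.** A knowledge item spans 1 − 0 = 1 point and a Likert item 5 − 1 = 4 points, a ratio of 1/4. With k knowledge, a attitude and p practice items, knowledge's share of the total's attainable range is k/(k + 4a + 4p). The item numbers below are assumptions.

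| k / a / p | Share of range |
|---|---|
| 5 / 10 / 10 | 5/85 = 5.9% |
| 10 / 10 / 10 | 10/90 = 11.1% |
| 10 / 5 / 5 | 10/50 = 20% |
| 20 / 10 / 10 | 20/100 = 20% |
| 20 / 5 / 5 | 20/60 = 33.3% |
| 40 / 5 / 5 | 40/80 = 50% |

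**Step 4. Range is not influence.** Knowledge's share of the total's variance was also computed. The assumptions were knowledge items answered correctly half the time (variance 0.25), a Likert SD of 0.8 to 1.2, an inter-item correlation within each part of 0 to 0.3, and independent parts. A part with n items of variance v and correlation ρ has variance v(n + n(n − 1)ρ). The shares are 8–16% for 10/10/10, 15–40% for 10/5/5 and 26–70% for 20/5/5. For example, the lowest value for 10/10/10 is 2.5/(2.5 + 14.4 + 14.4) = 8.0%, with SD 1.2 and ρ = 0. The weight of knowledge thus depends heavily on a design that is not yet fixed.

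**The case against.** The strongest reply is that the text never says *do not know* should earn a mark. It lists that answer separately and gives it 0, which suggests the authors meant it as not correct. If reversal swaps only *yes* and *no*, the fault disappears, as the last column of the first table shows. This stands as an account of likely intent. It does not clear the rule, because the protocol does not exempt *do not know* from reversal and the ordinary operation on the stated codes produces the fault.

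A second reply is that the questionnaire is unfinished and that item keys belong in a manual or analysis plan. The absence of item counts is indeed no fault in an article. But the article does state a coding and a total, and it is that stated rule which misbehaves. Testing reliability and validity does not in itself set an answer key or weights.

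Third, a total could be formed for each part, and the mixed-scale point would then fall away. This is possible, though the singular score in the Analysis strategy and Discussion sections favours one total. A KAP total is also a composite by design, so a low weight for knowledge is a weakness of weighting and does not make the score meaningless. Equal weights after rescaling are a convention too.

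A reader might infer that this primary outcome hardly measures knowledge, or that the intervention's effect on knowledge is hidden. The documents support neither. Only some items are reversed, the others register gains correctly, and knowledge's share could be as high as half of the range. A reader might also infer that the total mostly reflects desirable answering by cooks who know their group. The Randomization and blinding section says participants will be blinded. Whether that is achievable is a separate question, and this point does not rest on it.

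**Conclusion.** The point holds as a defect in a stated rule with a bounded but unknown effect.

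- Applied as written, reverse coding gives *do not know* the mark of a correct *no* on the reversed items, and learning the right answer adds nothing there. The dilution equals the reversed fraction of knowledge items if such gains are evenly spread. It is zero if the authors meant to hold *do not know* at 0.
- If one raw total is meant, each knowledge item has one quarter of the range of a Likert item. Knowledge's share of the range is about 6% to 50% over the assumed splits, and 11% only under equal item numbers.

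It deserves correction because KAP is a primary outcome and the change costs almost nothing. It does not show that the outcome is invalid.

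**What to change.** 1. Score each knowledge item against its answer key: correct = 1, incorrect or *do not know* = 0, including items where *no* is correct. Drop the reverse-coding step for knowledge.
2. Store *yes*, *no* and *do not know* as three distinct raw values, so that scores can be rebuilt.
3. Report knowledge, attitude and practice scores separately. If a total is kept, first put the three on a common scale, for example 0–100 each, and take the mean. Knowledge then carries one third of the range whatever the item numbers.

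The cost is a change to the wording and the scoring syntax before data collection, with no added burden on participants. The total is no longer a raw sum, so it would not be directly comparable with raw KAP sums, and the equal weighting should be stated as a choice.
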